## Abstract

**Background:**

Thromboembolism (TE) and infection are two common complications of central venous line (CVL). Thrombotic CVL-dysfunction is a common, yet less studied, complication of CVL. Two retrospective studies have reported significant association of CVL-dysfunction and TE. Recent studies indicate association of CVL-related small clot with infection. Infection is the most common cause of non-cancer related mortality in children with cancer. We and others have shown reduced overall survival (OS) in children with cancer and CVL-dysfunction compared to those without CVL-dysfunction. Despite these observations, to date there are no prospective studies to evaluate the clinical significance of CVL-dysfunction and it’s impact on the development of TE, infection, or outcome of children with cancer.

**Study design:**

This is a prospective, analytical cohort study conducted at five tertiary care pediatric oncology centers in Ontario. Children (≤ 18 years of age) with non-central nervous system cancers and CVL will be eligible for the study. Primary outcome measure is symptomatic TE and secondary outcomes are infection, recurrence of cancer and death due to any cause. Data will be analyzed using regression analyses.

**Discussion:**

The overall objective is to delineate the relationship between CVL-dysfunction, infection and TE. The primary aim is to evaluate the role of CVL-dysfunction as a predictor of symptomatic TE in children with cancer. We hypothesize that children with CVL-dysfunction have activation of the coagulation system resulting in an increased risk of symptomatic TE. The secondary aims are to study the impact of CVL-dysfunction on the rate of infection and the survival [OS and event free survival (EFS)] of children with cancer. We postulate that patients with CVL-dysfunction have an occult CVL-related clot which acts as a microbial focus with resultant increased risk of infection. Further, CVL-dysfunction by itself or in combination with associated complications may cause therapy delays resulting in adverse outcome.

This study will help to identify children at high risk for TE and infection. Based on the study results, we will design randomized controlled trials of prophylactic anticoagulant therapy to reduce the incidence of TE and infection. This in turn will help to improve the outcome in children with cancer.

## Background

Cancer is the leading cause of disease-related death in North American children [1,2]. Intensive therapy has resulted in over 80% of cure-rates in children with cancer, but therapy-related toxicity can limit the dose intensification of chemotherapeutic agents and compromise the prospect for cure [3]. Thus, it is important to minimize or prevent therapy-related complications.

Thromboembolism (TE) is a common and potentially fatal complication in children with cancer with up to 16% prevalence of symptomatic and ~ 40% of asymptomatic TE [4-10]. A recent population-based study showed dramatic increase in the incidence of TE in hospitalized children in the USA [4]. Cancer is a major underlying disease in children with TE and accounts for ~ 40% of pediatric TE [4-7]. We estimate that the risk of TE in children with cancer is at least 600-times higher than that in the general pediatric population [8-10].

TE is associated with significant morbidity, mortality and financial burden. The majority of symptomatic TE in children with acute lymphoblastic leukemia (ALL) occurs in potentially fatal sites; ~ 50% in the central nervous system (CNS) in the form of arterial ischemic stroke or sinovenous thrombosis, 2% pulmonary embolism (PE) and 2% in the right atrium [8,9]. A recent population based study showed that children with cancer are at increased risk of recurrent TE. Development of TE in children with cancer also leads to prolonged hospitalization and increased mortality [4]. The average case fatality ratio from TE in children with ALL is reported to be 15% [8,9]. In addition, the development of TE interferes with the scheduled therapy and therapy interruptions are known to compromise cure rates [10,11]. The estimated direct medical care cost of adult TE in the USA is ~ $600 million/year [12]. Although similar estimates are unavailable for children, development of TE undoubtedly adds to the direct and indirect therapy cost.

Thus, TE is a growing and significant problem in children with cancer. TE can be treated with anticoagulant therapy. Hence it is important to have reliable methods for early diagnosis of TE. In addition, TE is preventable with anticoagulant prophylaxis, even in children with cancer [13,14]. To avoid mortality and morbidity related to TE it is important to identify children at high risk for development of TE. However, the risk factors predisposing children with cancer to TE are yet to be defined.

Central venous line (CVL) is the single most important risk factor for development of TE in children [15-29]. Long-term CVL has become an integral part of cancer-therapy in children. It has improved both the quality of care and quality of life in children with malignancy. CVLs are commonly used to deliver chemotherapy, blood products, parenteral nutrition and other intravenous therapies as well as facilitate repeated blood drawing essential for the care of these patients. However, CVLs are associated with significant complications leading to morbidity and mortality [16-29]. Two recent studies have identified a CVL-related complications rate of 40%-46% in children with cancer [18,19]. Infection and TE are the two most common and serious medical complications related to CVL and may necessitate CVL removal in ~ 20%-35% of tunneled CVLs [29].

CVL-related TE is associated with significant acute and chronic morbidity and mortality. Catheter occlusion (in 11-40% patients), loss of venous access, infection (22-40%), embolism to other vessels including PE (~13%), and subsequent development of post-thrombotic syndrome (15-35%) are commonly described morbidities in patients with CVL-associated TE [21,23,25,30]. As observed in a recent study, patients with CVL-related TE had shorter CVL life and increased number of CVLs compared to those without TE [19]. Further, CVL-related thrombi may promote TE at other sites in the body. In addition, CVL-related acute morbidities lead to loss of CVL and interruption of chemotherapy [19-31]. Using a retrospective cohort design we and others have shown an adverse impact of CVL dysfunction on survival of children with cancer [32,33].

### Significance of CVL dysfunction

CVL-dysfunction (also known as occlusion or malfunction) is a common, but relatively less studied complication of CVL. Various studies defined dysfunction as the inability to infuse fluids and/or withdraw blood and can be mechanical or thrombotic [17,18,22,32,34]. The thrombotic occlusion is thought to be resulting from small clot at the tip or surrounding the tip of the CVL. Dysfunction can be partial where infusion is possible but blood cannot be aspirated or complete with inability to either aspirate or infuse. In a prospective study of adults with cancer, Lee et al., have documented 11% prevalence of CVL-dysfunction; interestingly patients with CVL-dysfunction had a significantly higher risk of developing symptomatic CVL-related TE (OR 14.7, p<0.001) [34].

In comparison to adults, studies in children with cancer have reported much higher prevalence of CVL-dysfunction ranging from 21%-39% [17,18,32,33,35]. Although, the higher prevalence of CVL-dysfunction observed in these studies may be related to the smaller sample size and retrospective study-design, physiologically, children are likely to be more susceptible for CVL-dysfunction due to the smaller vascular dimensions and higher CVL to vessel diameter ratio [35,36]. In fact the observation of higher risk of CVL-related complications in younger children supports this notion [17-20]. Three retrospective studies (including ours) have evaluated the risk of TE in children with cancer and CVL-dysfunction; all three studies have shown significantly increased risk of TE in children with CVL-dysfunction [17,32,33,36].

We propose a prospective, multicenter, cohort study to evaluate the role of CVL-dysfunction as a predictor of TE and to study the impact of CVL-dysfunction on the frequency of infection and outcome of children with cancer. We will also evaluate the impact of CVL-related (type, insertion techniques and care guidelines) and patient-related (age, height, body mass index) factors on the incidence of CVL-dysfunction, TE and infection. We plan to conduct this study in five tertiary care pediatric oncology institutions. The participating institutions are members of the Pediatric Oncology Group of Ontario (POGO) and are responsible for the diagnosis and therapy of all children with cancer in the province of Ontario.

The primary research question is as follows:

Do children with CVL dysfunction have increased risk of symptomatic thromboembolism compared to those without CVL dysfunction, while on cancer therapy?

### Primary hypothesis

Children with CVL-dysfunction are at increased risk for diagnosis of symptomatic TE while on therapy for cancer compared to those without CVL-dysfunction.

### Secondary hypotheses

1. Children with cancer and CVL-dysfunction have an increased prevalence of infection compared to those without CVL-dysfunction. Presence of both CVL-dysfunction and infection increases the risk of TE in children with cancer.

2. Children with cancer and CVL-dysfunction have decreased OS and EFS compared to those without CVL-dysfunction.

### Aims

The overall objective of the study is to explore the relationship of CVL-dysfunction, TE and infection in children with cancer and to study the impact of CVL-dysfunction on overall outcome in children with cancer.

### Primary aim

To compare the risk of symptomatic TE in children with or without CVL-dysfunction while receiving therapy for cancer.

### Secondary aims

In children receiving therapy for cancer,

1. To compare the prevalence of infection at any site in children with or without CVL-dysfunction

2. To compare the five-year OS and EFS in children with or without CVL-dysfunction

3. To delineate the relationship of CVL-dysfunction, infection and TE

4. To evaluate the impact of different CVL-related (type, insertion techniques, care guidelines) and patient-related (age, height, body mass index) factors on the development of CVL-dysfunction, TE and infection

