Thus, there is no reliable, safe, inexpensive and noninvasive screening tool for diagnosis of CVL-related TE in children. Hence one may have to consider surrogate markers as predictors of underlying TE. An ideal predictor will reliably identify patients with high a probability of underlying TE for whom evaluation by invasive tests will be justified. Considering available evidence, we propose that CVL-dysfunction may be a good predictor of underlying TE. If indeed the presence of CVL-dysfunction can predict TE then such patients could be evaluated further with the gold standard test of venography and treated with anticoagulation therapy. This in turn will reduce the risk of development of symptomatic TE and infection. However, the first step is to confirm the presence (and the strength) of association of CVL-dysfunction and TE in a large prospective study.

#### Rationale for secondary aim 1

Bacterial and fungal infections and sepsis are well-known complications in children undergoing intensive chemotherapy. Presence of CVL increases the risk of infections [17-19,41-43]. Two recent prospective studies conducted in children with cancer and hematological disorders reported infection rates of 0.87 and 1.7/1000 catheter-days [18,19]. In one study, 40% of patients had CVL-related infections and 44% of the episodes required CVL removal [43].

Although the association of CVL with infections has been well documented, only recently investigators have begun to explore the correlation of CVL-related infection with underlying local TE [42,43]. Prospective studies conducted in adult patients have shown that the local or systemic CVL-related infections are likely to increase the risk of TE in patients on therapy for cancer [42,43]. A retrospective study showed increased risk of thrombosis in children with cancer and documented infection [odds ratio (OR) 2.2, p = 0.016] [17]. So far there is no prospective study to evaluate the relationship of TE and infection in children with cancer.

#### Rationale for secondary aim 2

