##### Details of CVL insertion

Details of CVL insertion (including the date, body side, type of CVL used, type of procedure, and any difficulty encountered) will be recorded. For patients requiring more than one CVL during the course of initial cancer therapy, details of each additional CVL will be recorded separately. The life span of the CVL will be measured in “catheter-days” calculated from the time of insertion and time of removal of CVL or the time of death or last follow-up if the CVL was still in place.

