##### Analysis plan

The analysis and reporting of the study will be performed in accordance with the STROBE Statement [50]. The primary outcome is a binary variable- symptomatic TE (presence/absence) as well as a continuous variable (time to event). Independent variables include: age, number of catheter days and time to CVL-dysfunction as continuous variables and, gender (male/female), cancer type, CVL-dysfunction (presence/absence), symptomatic TE (presence/absence), infection (presence/absence) as categorical variables. The process of participant recruitment and retention will be summarized using a flow diagram. Analysis results of participant recruitment and retention will be summarized using descriptive summary measures: mean (standard deviation) or median (minimum-maximum) for continuous variables; and number (percent) for categorical variables. We will use logistic regression analysis to determine the factors that can best discriminate between the two patient groups (i.e. those with and without TE). The list of potential factors is determined *a priori* and includes age of the patient at the time of diagnosis of cancer, cancer type; CVL-dysfunction (presence/absence), infection (presence/absence) and CVL type (internal/external). Univariate analyses will be performed to determine which variables to include in the multivariable models using the criterion of alpha = 0.20. Initially, we will use complete case analysis (i.e. do the analysis without taking missing data into account) and then repeat the analyses with missing data handled by multiple imputation technique [51-53].

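### Secondary aim 1 compares the prevalence of infection by CVL-dysfunction without tying it to catheter time or to the order of events, while the article elsewhere calls the same outcome a rate or a frequency

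*Protocol article*

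**What the plan says.** The measure is stated twice as a prevalence. Secondary hypothesis 1 reads "Children with cancer and CVL-dysfunction have an increased prevalence of infection compared to those without CVL-dysfunction", and secondary aim 1 is "To compare the prevalence of infection at any site in children with or without CVL-dysfunction".

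Two other places name the same outcome differently. The Discussion part of the abstract says "The secondary aims are to study the impact of CVL-dysfunction on the rate of infection and the survival". The section on the significance of CVL dysfunction says the study is "to study the impact of CVL-dysfunction on the frequency of infection and outcome of children with cancer". The rationale for secondary aim 1 cites two prospective studies that "reported infection rates of 0.87 and 1.7/1000 catheter-days".

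The Analysis plan lists "infection (presence/absence) as categorical variables" among the independent variables. The same sentence lists catheter-days and time to CVL-dysfunction as continuous independent variables. Neither is in the a priori factor list that follows, and the only logistic model described has symptomatic TE as its outcome. No model is described for infection.

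On timing, the section on measuring the exposure classes a child as exposed only from the point at which the dysfunction definition is fulfilled, and that definition needs two or more documented occasions. Follow-up for TE ends with each child's own end of therapy and final line removal. Line life span is recorded in catheter-days, "calculated from the time of insertion and time of removal of CVL", or to death or last follow-up if the line is still in place.

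**The concern.** Infection can recur, and it accrues with time on a line. So does dysfunction. If line duration differs between children, those with longer lines have more opportunity for both, and comparing the proportion ever infected mixes time at risk with any effect of dysfunction.

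Order is a separate problem. The postulated mechanism is that an occult clot behind the dysfunction acts as a focus for infection, so only infections after onset of dysfunction bear on it. The rationale for secondary aim 3 also allows the reverse path, from infection to clot to dysfunction, and says the chronology is unclear. A prevalence comparison cannot tell these paths apart.

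The Discussion says that confirming the association of dysfunction, TE and infection would support identifying children at high risk of infection and prophylactic strategies, with anticoagulation as the example. An excess produced by line duration should not feed into that.

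**Working it through.** **The plan's own figures.** The article gives no figure for the infection aim. Its general figures reproduce: 450 × 0.20 = 90 exposed and 360 unexposed; 450 × 0.11 = 49.5, the stated approximate 50 TE events.

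**Inputs from the article.** Infection rates of 0.87 and 1.7 per 1000 catheter-days; 20% exposed; 90 against 360 children; alpha 0.05 (taken as two-sided).

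**Assumed, because the article does not give them.** Line durations, the shape of both hazards over time, and independence of dysfunction and infection (the null). The cited rates stand in for infection at any site.

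**Step 1: prevalence against line time at a constant rate.** P(ever infected) = 1 − exp(−rate × days / 1000).

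| Catheter-days | 0.87 per 1000 | 1.7 per 1000 |
|---|---|---|
| 180 | 14.5% | 26.4% |
| 365 | 27.2% | 46.2% |
| 730 | 47.0% | 71.1% |
| 900 | 54.3% | 78.3% |

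Repeat episodes, lost under ever/never coding, are 1 − P(ever)/(rate × days / 1000): 7% to 31% of episodes at the lower rate and 14% to 49% at the higher, over 180 to 900 days.

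**Step 2: odds ratio with no true effect, constant hazards.** The dysfunction hazard is set so that 20% are ever exposed. One case by hand: half the lines last 180 days and half 800, infection rate 0.87.
- P(ever infected) is 0.145 at 180 days and 1 − exp(−0.696) = 0.501 at 800.
- Mean duration comes out at 673 days in the exposed and 444 in the unexposed, so the share with long lines is (673 − 180)/620 = 0.795 and (444 − 180)/620 = 0.426.
- Exposed prevalence: 0.205 × 0.145 + 0.795 × 0.501 = 0.428. Unexposed: 0.574 × 0.145 + 0.426 × 0.501 = 0.297.
- OR = (0.428/0.572)/(0.297/0.703) = 1.77.

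All cases, with ranges over the two cited rates; the last column is the chance of a falsely significant excess with 90 against 360 children (total of 450):

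| Assumed durations | OR under the null | False excess |
|---|---|---|
| All equal | 1.00 | 2.5% (nominal) |
| Uniform 90–365 days | 1.17–1.18 | 8–10% |
| Uniform 120–900 days | 1.32–1.42 | 21–31% |
| Half 180, half 800 days | 1.77–2.07 | 66–86% |
| 0.5/1/2.5 years (30/20/50%) | 1.65–1.92 | 56–74% |
| Half 0.5, half 2.5 years | 1.94–2.34 | 79–92% |

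The last two rows use a Wald test on the log odds ratio, the others a two-proportion test.

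**Step 3: hazards concentrated early.** Let both hazards be three times higher in the first 180 days, with the average infection rate held at the cited values. The 0.5/1/2.5-year case falls to an OR of 1.20–1.26 (false excess 12–16%) and the half/half 0.5 and 2.5-year case to 1.26–1.33 (15–23%). With a fivefold early excess the 0.5/1/2.5-year case gives 1.10–1.13 (6–7%).

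**Step 4: order.** In the constant-hazard null simulation, among children with both dysfunction and infection, the first infection came before dysfunction in 50% to 57%.

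**Step 5: does splitting time at onset cure it?** With constant hazards, episodes per catheter-day before and after onset give a rate ratio of 0.995 to 1.01 in every case. With the threefold early excess, the same ratio without adjustment for time since insertion is 0.73 to 0.83, a spurious protective effect, because exposed time is later time.

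**The case against.** The strongest reply is that the article does not describe a crude ever/never analysis of infection. It gives no model for aim 1. The presence/absence coding sits in a list of independent variables. Catheter-days and time to dysfunction appear in that list too, as does cancer type, which plausibly tracks therapy length. The abstract already says rate. A fuller plan may hold the rest.

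Part of this stands: the absence of a model in an article is not the point, and the coding line does not by itself fix the aim 1 outcome. But the hypothesis and the aim do name the measure, and that measure conflicts with the abstract and the background. Adding total catheter-days as a covariate would still leave order and repeat episodes unresolved. Secondary aim 3 covers the relationship of the three complications but states no method for their sequence.

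A reader might go further and infer that prevalence here mainly reflects how long the line stayed in, or that aim 1 is likely to appear confirmed even without an effect. The article does not support either. Those readings need widely spread durations and roughly constant hazards, and it states neither. Nor does the Discussion rest the anticoagulant trial on aim 1 alone: it ties that trial to the primary TE hypothesis, and its sentence on infection requires the association of all three complications. The abstract does, however, name infection as a target of the later trials.

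**Conclusion.** The point holds as an inconsistency in the stated measure and a weakness in the one that the aim names. Taken at its word, aim 1 counts infections before dysfunction as exposed, discards repeat episodes and leaves time at risk uncontrolled. In every unequal-duration case examined, the resulting bias favoured the hypothesis.

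Its size is an assumption throughout. With no true effect the odds ratio is 1.00 for equal durations, about 1.05 to 1.4 for moderate spread or early-concentrated hazards, and about 1.6 to 2.4 only for roughly fivefold spread with constant hazards. The chance of a false excess runs correspondingly from nominal to about 90%. Equal durations remove the time-at-risk bias but not the problem of order. This is a secondary aim and the remedy is cheap, so it should be corrected, but it does not threaten the study.

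**What to change.** Use one term for the aim 1 outcome in the abstract, background, hypothesis and aim, and define it as infection episodes over catheter time. Treat dysfunction as a time-varying exposure that starts when the definition is met, so that earlier infections and catheter-days count as unexposed.

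Analyse with an Andersen-Gill model on time since CVL insertion with robust standard errors. A count model with a catheter-day offset is acceptable only if it also adjusts for time since insertion; Step 5 shows why the offset alone is not enough. Report prevalence by group as description.

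The cost is analysis wording, a rule for when a new infection episode starts, and confirmation that infection dates are captured. Catheter-days, infection details and time to dysfunction are already planned.
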